### Study aims and objectives

The aims of this trial are to evaluate whether bodily disturbances in post-treatment cancer patients can be improved by group BPT, and to estimate the efficacy of intermittent smartphone-triggered bodily interventions (German acronym ‘KPTK: **K**örper**p**sycho**t**herapie bei **K**rebs’ in English: BPT for cancer patients. For trial registration data see Additional file 1). We assume that bodily disturbances will improve from pre- to post-BPT in post-treatment cancer patients. Furthermore, participants will show better immediate outcomes with regard to mood and bodily well-being if they receive smartphone-triggered bodily interventions as compared to smartphone-triggered control interventions. With this non-randomized evaluation of a weekly group BPT using a waiting-period comparator, with a nested randomized controlled trial (RCT) we will primarily obtain information on the efficacy of the intervention. Furthermore, we will be able to investigate intervention effects and mechanisms of action in more detail, together with acceptance and perception of the intervention, unwanted effects and burden to patients.

The primary objective of the planned project is to evaluate whether group BPT is related to reduction of bodily disturbances in post-treatment cancer patients.

Secondary objectives of the project are
to assess if BPT is related to more body awareness/mindfulness;to estimate, whether intermittent smartphone-triggered bodily interventions go along with immediate improvements in bodily well-beingto evaluate, whether BPT is related to improvements in mental well-being (anxiety, depression, somatization, pain, etc.) and quality of life;to assess group processes/cohesion;to assess aspects of the intervention, such as
recruitment and inclusion;undesired side effects (‘safety assessment’);from the patients’ perspectives:
(i)acceptance and burden of the intervention (this assessment is recommended according to recent initiatives, such as ‘Partnering with Patients’ launched by the British Medical Journal (BMJ) [37]);(ii)suggestions for improvement of the intervention.

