#### Smartphone-triggered interventions

The smartphone-triggered bodily interventions consist of brief BPT exercises aiming at supporting the transfer from the group BPT sessions into patients’ daily lives. Smartphone bodily interventions are triggered by short audio-clips, as described elsewhere [51]. The patients are asked to log into the system each day once. Then, they randomly receive either an audio-clip triggering a bodily intervention (3 times a week) or a control intervention (3 times a week). In case of technical difficulties, participants can contact the study team. The content of the bodily interventions is outlined in Table 2. The control interventions consist of 15 selected fairy tales all adapted approximately to the same length as the bodily interventions. The advantage of fairy tales is their universality and distance to the content of cancer diagnosis or its treatment. The smartphone-triggered bodily and control interventions are provided over a period of 5 consecutive weeks on 6 days per week, in parallel to the BPT sessions. Thus, each patient undergoes 15 bodily and 15 control interventions.

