### Assignment of smartphone-triggered interventions

An independent party (Clinical Trial Unit (CTU) of the University Hospital Basel) generated the computer-generated random sequences, using the software R, allowing individual randomization of every training day of each trial participant to the bodily or control interventions (within-subject randomization). Randomization was blocked every six training days for each trial participant to ensure that during each training week, each subject is triggered for three bodily and three control interventions of the pre-specified 6 weekly exercises per trial participant over the 5 consecutive weeks. No further restrictions applied. The series of random sequences generated by CTU was provided to a collaborator, who sequentially linked each patient after enrolment with the next sequence on the list. Trial participants were blinded to randomization up until the moment at which the intervention was provided; Body psychotherapists (care providers) were blinded to randomization. Outcome assessment on each smartphone-based intervention day was conducted directly via smartphone, so outcome assessor blinding is not applicable.

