### Sample size estimation

Sample size of the planned project is based on an a priori power analysis. With 52 participants completing the group BPT (study site Basel: *n* = 26, study site Winterthur: *n* = 26), we will have sufficient power (1-*β* = 0.94) to gain pre-post differences of medium effect size (*d* = 0.5) in the primary outcome. Allowing for a 30% dropout rate and including a safety margin of 10% accounting for unexpected variation in our estimates, we aim to include a total of *N* = 88 patients. With regard to the nested RCT evaluating the short-term efficacy of smartphone-triggered bodily interventions, power analysis is more demanding. Given a maximum of 15 bodily interventions and 15 control interventions per person and assuming a participation rate in daily interventions of 80% (which is a rather conservative estimate, as compared to the previously observed 96% participation rate in an earlier study [51]), we expect on average a total of 24 completed smartphone-triggered interventions per participant. Assuming a correlation of 0.5 among repeated measures and a nonsphericity correction ε of 1, we expect sufficient power (1-*β* > 0.99) to detect medium effect sizes (*f* = 0.25) (estimation conducted using G*Power 3.1 [69], based on an analysis of variance (ANOVA) model with repeated measures and within factors).

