### Statistical and content analyses

Descriptive analyses of continuous variables will include the calculation of central tendency and dispersion; descriptive analyses of categorical variables will include numbers and frequencies.

We intend to use inferential statistics to compare outcomes and parameters over time: (1) from baseline to post group BPT intervention and (2) from pre to post smartphone-triggered bodily intervention. We intend to compare changes from T1 to T2 with changes from T0 to T1. Therefore, we intend to use mixed effect generalized linear models, which will also be used to assess potential mediators of therapeutic changes. Baseline equivalence between T0 and T1 will be assessed in order to adjust potential baseline differences and that way to reduce potential bias arising from the nonrandomized study design. We intend to conduct additional analyses, including adjusted (e.g., age, gender) and subgroup analyses (e.g., cancer entity, BPT group composition, level of somatic distress). All statistical tests will be two-sided, and *p*-values ≤0.05 will be considered statistically significant. In the event of multiple comparisons, Bonferroni-Holm corrections will be carried out.

We intend to analyze qualitative data based on thematic analyses, aiming at identifying themes within the data and at establishing meaningful categories, their interrelation, and their relation to the outcomes of the intervention [68, 70].

Intention-to-treat analyses will include all patients being enrolled in the study and randomized. Per protocol analyses will follow an all-patients-receiving-intervention perspective. Whenever appropriate, we are going to use multiple imputation methods [71].

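### The analysis section names the smartphone comparison only as pre-to-post change with the bodily clips, not as the bodily-versus-control contrast that the hypothesis and the day-level randomisation call for

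*Protocol article*

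**What the plan says.** All references are to the protocol article.

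- **Study aims and objectives.** Participants are expected to have better immediate mood and bodily well-being "if they receive smartphone-triggered bodily interventions as compared to smartphone-triggered control interventions". The matching secondary objective, in the same section, asks only whether the bodily interventions are accompanied by immediate improvement and names no comparator.
- **Smartphone-triggered interventions.** "Thus, each patient undergoes 15 bodily and 15 control interventions". The comparator is an active audio control: "The control interventions consist of 15 selected fairy tales all adapted approximately to the same length as the bodily interventions".
- **Assignment of smartphone-triggered interventions.** The design provides for "individual randomization of every training day of each trial participant to the bodily or control interventions (within-subject randomization", blocked by six training days so that each week holds three of each type.
- **Sample size estimation.** The nested RCT is powered on 24 expected completed interventions per person, which is 80% of 30 and so counts both types. The model is a repeated-measures ANOVA with within factors; the bodily-versus-control contrast is not named.
- **Statistical and content analyses.** Two comparisons over time are listed. The smartphone one is "2) from pre to post smartphone-triggered bodily intervention". The only contrast of changes in the section is "We intend to compare changes from T1 to T2 with changes from T0 to T1", which concerns group BPT. The mixed models are introduced directly after that sentence.

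**The concern.** The hypothesis is comparative and the randomisation supports it, but the one comparison written down for the smartphone part is within a single condition. A pre-post change on bodily days answers whether people feel better after a bodily clip. It does not answer whether they feel better than after a fairy tale of similar length.

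The ratings are self-reported immediately before and after a clip of 10 to 15 minutes, and participants know which type they have received once it is provided. Some change from rest, attention or expectation is plausible with either type. The control days exist to remove it. This is also the only randomised comparison in the trial, since group BPT is evaluated without randomisation. An analyst who followed the section to the letter would give an uncontrolled answer to the one question the trial can answer with a randomised control.

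**Working it through.** **1. The plan's own figures.**

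Nested RCT, noncentral F for a within-factor repeated-measures ANOVA, with n = 52 ("With 52 participants completing the group BPT"), m = 24, f = 0.25, correlation 0.5, ε = 1:

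- λ = f²·n·m/(1 − ρ) = 0.0625 × 52 × 24 / 0.5 = 156
- df = 23 and 51 × 23 = 1173
- power > 0.9999; the plan states more than 0.99.

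Primary outcome, paired t with n = 52, d = 0.5, two-sided 0.05: power 0.943; the plan states 0.94.

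Both figures reproduce. The first, however, is for a factor with 24 levels, not for the one-degree-of-freedom bodily-versus-control contrast.

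**2. What the named test does when there is no specific effect.**

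The following inputs are assumptions and are not in the documents. The unit is the SD of daily pre-post change (= 1). Both audio types produce the same mean change δ. The 24 completed days split evenly, giving 12 bodily days per person. The between-person SD of change, s, is 0.3 or 0.5.

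One-sample t on participant means: dz = δ/√(1/12 + s²), noncentrality dz·√52, two-sided 0.05.

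- s = 0.3: √(0.0833 + 0.09) = 0.416
- s = 0.5: √(0.0833 + 0.25) = 0.577

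| Shared change δ | s = 0.3 (formula) | s = 0.5 (formula) | Simulation |
|---|---|---|---|
| 0 | 5% | 5% | 5% |
| 0.1 | 40% | 23% | 22% |
| 0.2 | 92% | 69% | 67% |
| 0.3 | >99% | 96% | 95% |

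The simulation (4,000 runs per row) used person SD 0.5 plus a person-by-condition SD of 0.3, half of which falls on each condition. That is why it sits slightly below the s = 0.5 column. In the same runs, and in a further scenario at δ = 0.5, the paired bodily-versus-control test rejected in 4.6% to 5.3%.

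**3. Whether the randomised contrast is feasible at the planned size.**

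With one mean per condition per person, m = 2, f = 0.25 and ρ = 0.5: λ = 0.0625 × 52 × 2 / 0.5 = 13, df 1 and 51, power 0.943. This equals dz = 0.5. For smaller effects, dz = 0.3 gives 0.56 and dz = 0.2 gives 0.29. If instead the 0.5 correlation applies to single days and the effect does not vary between people, power exceeds 0.99.

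**The case against.** The strongest reply is that the list is shorthand. Its sentence concerns comparisons over time, and bodily versus control is a comparison between conditions, so its absence from that list does not show that it will not be made. Item (1) is equally abbreviated: it omits the waiting-period comparator, which the next sentence supplies. The hypothesis, the randomisation and the inclusion of control days in the 24 expected interventions all point to the randomised contrast. The mixed models could carry a condition term, and model terms are commonly left to an analysis plan, which is not shown here.

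Much of this stands. A reader might infer that the investigators mean to discard the control days, or that the randomised contrast will certainly not be estimated. The document does not support that: its aims and sample-size sections show that the contrast was intended.

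What does not stand is that the matter is only missing detail. The section is not silent. It names a comparison for the smartphone part, and that comparison cannot test the stated hypothesis. The following sentence supplies a comparator for item (1) and none for item (2), and the mixed models are tied to the T0–T1–T2 comparison. The secondary objective, worded without a comparator, makes the uncontrolled reading easier to adopt.

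It is also fair to object that no single percentage should be quoted. The 92% at 0.2 SD depends on the smaller between-person SD; other plausible inputs give 67%, and at 0.1 SD the range is 22–40%.

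**Conclusion.** The concern holds as an internal conflict. The analysis section fixes a within-condition comparison where the hypothesis and the design require a between-condition one. Taken literally, the named test attributes any shared improvement to the bodily clips. False-positive rates are roughly 22–40%, 67–92% and 95% or more for shared changes of 0.1, 0.2 and 0.3 SD, against about 5% for the randomised contrast. These rates rest on the assumed variances, the even split of days and the assumed shared change. The direction of the error does not depend on them.

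The consequence is confined to a secondary objective. Neither the primary outcome nor its sample size is affected, and no stated power figure is numerically wrong.

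**What to change.** Restate item (2) as the difference between bodily and control days in immediate pre-to-post outcome, estimated over all randomised training days in a mixed model with participant random effects. Post score adjusted for that day's pre score, or a condition-by-time term, would each serve; the exact covariates and random-effect structure are a choice among several acceptable ones. Base the nested-RCT efficacy conclusion on that contrast and report within-condition pre-post change descriptively. Add the comparator to the wording of the secondary objective so that it agrees with the hypothesis. It would also help to restate the nested-RCT power for the one-degree-of-freedom contrast: 0.94 to above 0.99 for the stated medium effect, depending on the correlation structure.

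The cost is wording only. Pre and post ratings around the smartphone interventions are already scheduled, so no patients or assessments are added. The change should be made before the smartphone data are analysed.

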### Safety aspects and monitoring

If an adverse event occurs. The project leader is promptly notified if immediate safety and protective measures have to be taken during the conduct of the research project. The Ethics Committee will be notified of these measures and of the circumstances necessitating them within 7 days. If a serious adverse event occurs, the research project will be interrupted and the Ethics Committee notified on the circumstances within 7 days according to HRO Art. 21.An independent party monitors the study (Category A according to ordinance HRO Art.7).

## Discussion

The treatment of cancer patients is a major challenge and often relies on administering medication such as cytotoxic agents [7]. In most cases these treatments go along with physical and psychological distress and additional approaches are required to improve health related quality of life in cancer patients. In recent years, psychosocial interventions have gained increasing importance [72–75]. Therapies such as cognitive behavioral therapy (CBT) that have proven to be effective in non-cancer contexts often show little or no effects in cancer patients [76–79]. Additionally, studies assessing complementary interventions, such as music-based interventions or mindfulness-based stress reduction (MBSR), showed beneficial effects in cancer patients; yet results were often heterogeneous [80–84]. There is growing evidence that movement-based interventions for cancer patients (in terms of physical activity and exercise) are safe and feasible and improve quality of life. Effect sizes, however, are mostly small [85–91]. Some studies have applied body-related interventions in cancer patients, such as Tai Chi, acupressure, or Qi-Gong. Within a larger intervention program they were, however, of minor importance, which makes it difficult to draw any conclusions regarding the effects of these bodily interventions [92–94].

Furthermore, some of the above-mentioned studies which included movement-based interventions have successfully incorporated home-based exercises in addition to face-to-face interventions [93, 95]. Apart from being used in cancer treatment, those psychotherapeutic interventions have shown positive effects. Recent evidence indicates that the implementation of new mobile technologies, such as smartphones, may help to increase therapeutic efficacy, when applied within a blended psychotherapy approach [96–99]. However, to the best of our knowledge, smartphone-triggered bodily interventions have not yet been applied and assessed in the context of cancer on a daily basis over five consecutive weeks.

Overall, the proposed study has strong potential benefit for cancer patients, as it may pave the way for new therapeutic approaches to treat bodily disturbances, which persist despite tumor therapy. Through a better coping with the experience of bodily sensations and disturbances cross-linked with the emotional and cognitive experience, patients’ biopsychosocial well-being and quality of life might be considerably improved.

In conclusion, the intervention evaluated in this study has the potential to be of high scientific and social value, as it will provide the basis for more differentiated and evidence-based interventions to support cancer patients, regarding persistent bodily disturbances. This may not only lead to reduced suffering and impairment, but may also result in outcomes, such as better family functioning, social functioning, etc.. The intervention may be expected to be cost-efficient, due to its conceptualization as group therapy. It will contribute to our understanding of the applicability of BPT to physical illnesses in general, and beyond mental disorders. Moreover it will allow a better understanding whether and how new technologies can be successfully combined with classic therapeutic face-to-face settings (‘blended psychotherapy’). Further, it will improve our understanding of therapeutic mechanisms of BPT in cancer patients. It will provide all necessary information to conduct a subsequent international phase III RCT on the topic. Finally, this project will contribute to enhance interdisciplinary and integrative cancer research and will further support the growing number of cancer survivors from a more comprehensive perspective.

## Data Availability

With this manuscript we provide the study protocol but no patient data.
